## 9.1 Study assessments schedule

|                                                      | Identification | Baseline | Treatment | 3 days* | 7 Days*              | 28 days*  |
|------------------------------------------------------|----------------|----------|-----------|---------|----------------------|-----------|
| Enrolment                                     |                |          |           |         |                      |           |
| Screening form                                       | S              |          |           |         |                      |           |
| Eligibility form                                     |                | S        |           |         |                      |           |
| Informed consent form                                |                | S        |           |         |                      |           |
| Demographics                                         |                | S        |           |         |                      |           |
| Injury details                                       |                | S        |           |         |                      |           |
| Randomisation (Day 0)                                |                | S (last) |           |         |                      |           |
| Treatment                                     |                |          |           |         |                      |           |
| Treatment details                                    |                |          | S         |         |                      | MR        |
| Primary outcome                               |                |          |           |         |                      |           |
| FLACC (or revised FLACC)                             |                | Q        |           | Q       | Q ( primary ) | Q         |
| Secondary outcomes                            |                |          |           |         |                      |           |
| Recovery of mobility                                 |                |          |           | Q       | Q **                 | Q **      |
| Requirement for oral analgesia                       |                |          |           | Q       | Q                    |           |
| Resource use                                         |                |          |           |         |                      | Q         |
| Parent/ guardian Satisfaction                        |                |          |           |         |                      | Q         |
| Attendances at ED, Plaster Room, or Fracture clinics |                |          |           |         |                      | MR        |
| X-rays on affected limb                              |                |          |           |         |                      | MR        |
| Pressure ulcers/ fracture displacement               |                |          |           |         |                      | MR        |
| Removal of immobilisation                            |                |          |           | Q       | Q **                 | Q ** / MR |
| Safety                                        |                |          |           |         |                      |           |
| Adverse events                                       |                |          |           |         |                      | MR***     |

S = data collected in person/remotely by site staff

Q = data collected from parent/guardian via a self-completion questionnaire

MR = data collected from medical records

\*post randomisation

\*\*if not recovered/removed at previous timepoint

\*\*\*Adverse events followed up until no longer ongoing

## **9.2 Unscheduled visits**

Participants/parents/guardians may be seen at additional visits outside those contacts scheduled for the study, but these visits would be part of usual care. Any additional attendances will be recorded (from medical records) as part of the secondary outcomes.

## **9.3 Procedures for assessing efficacy**

Efficacy will be assessed by comparing the mean FLACC score on day 7 (after randomisation) between the two groups.

## **9.4 Procedure for assessing safety**

Adverse events and serious adverse events are discussed in Section 10. If the site research team have any concerns about a participant's wellbeing or safety during the course of the trial, this will be flagged to the patient's usual clinical team.

## **9.5 Participant/parent/guardian withdrawals**

Due to the short follow-up period, and these timepoints aligning with usual care follow-up for these patients, withdrawal is expected to be minimal. Ability to complete outcomes remotely, with reminders, will also assist with this. We have kept the tasks required for participation as simple and infrequent as possible to ensure convenience without detracting from important outcomes. We have ensured that as much data is collectable as part of standard care without trial treatment visits and utilising online and text message-based data collection where possible.

Excessive participant/parent/guardian withdrawal from follow-up has a negative impact on a study. Centres will explain the importance of remaining on study follow-up to parents/guardians, and that changes to planned treatment need not imply withdrawal from the study. Parents/guardians may wish to stop their child's study treatment, or there may be a clinical need to stop study treatment (as per section 6.3). If this occurs, the parent/guardian should continue to complete their questionnaires, and sites should continue to collect information from medical records as per the study assessments schedule.

If parents/guardians do not wish to continue receiving questionnaires, their decision must be respected, and usual clinical care will continue. Parents/guardians may withdraw their consent for the study at any time, without providing a reason for this. If

this occurs, this will be documented on a study completion/ discontinuation form and the patient notes.

If parents/guardians withdraw their consent to continue receiving questionnaires, they will be given the option for their routinely collected data to be shared with the study team. This will allow the site to continue collecting information from their medical records as per the study assessments schedule, to inform the secondary outcomes.

If the parent/guardian explicitly states their wish for their child to not contribute further data to the study, this will be recorded on the study completion/discontinuation form, and no further data will be collected from the participant/parent/guardian for the study. Although the parent/guardian is not required to give a reason for discontinuing their study treatment, a reasonable effort will be made to establish this reason while fully respecting their rights.

Any data collected up to the point of the participant's withdrawal will be retained, and used in the final analysis, and this is made clear to the patient at the time of consent.

## **9.6 Loss to contact**

Efforts will be made to contact parents/guardians, and questionnaires will be sent, for all follow-up timepoints, regardless of whether the parent/guardian has completed questionnaires at the previous time point. Two text message reminders will be sent per questionnaire time-point (at one and two days after the initial questionnaire is sent), plus a phone call reminder for the day 7 questionnaire, or paper questionnaires, if required. Questionnaires will be open for completion until the end of the trial. Date of completion will be collected and considered for the analysis. Questionnaires will close two weeks after the 28 day follow-up timepoint for the last recruited participant.

After the study closes, participants will be defined as lost to contact if no questionnaire data is available for one follow-up time point, and all subsequent stipulated follow-up time points.

## 10. Safety Reporting

ICH-GCP requires that both investigators and sponsors follow specific procedures when reporting adverse events in clinical studies. These procedures are described in this section.

### 10.1 Definitions

| Term                        | Definition                                                                                                                                                                                                                                                                                                                                                                                                                                                                                      |
|-----------------------------|-------------------------------------------------------------------------------------------------------------------------------------------------------------------------------------------------------------------------------------------------------------------------------------------------------------------------------------------------------------------------------------------------------------------------------------------------------------------------------------------------|
| Adverse Event (AE)          | Any untoward medical occurrence in a study participant. (refer to SOP PM004 Adverse Events and Serious Adverse Events for more details)                                                                                                                                                                                                                                                                                                                                                  |
| Unexpected AE/SAE           | An adverse event or serious adverse event which has not been pre-specified as expected.                                                                                                                                                                                                                                                                                                                                                                                                         |
| Serious Adverse Event (SAE) | An AE which is serious, defined as any untoward medical occurrence or effect that : 
 
• Results in death
 
• Is life-threatening*
 
• Requires hospitalisation or prolongation of existing inpatients' hospitalisation**
 
• Results in persistent or significant disability or incapacity
 
• Is a congenital anomaly/birth defect
 
• Is otherwise considered medically significant by the investigator***
 
 |
| Related AE/SAE              | An AE or SAE which is related to a research procedure                                                                                                                                                                                                                                                                                                                                                                                                                                           |
| Notable Event               | An event of particular interest that does not necessarily meet the criteria for seriousness but requires expedited reporting as per the protocol.                                                                                                                                                                                                                                                                                                                                               |

\*The term life-threatening in the definition of a serious event refers to an event in which the patient is at risk of death at the time of the event; it does not refer to an event that hypothetically might cause death if it were more severe, for example, a silent myocardial infarction.

\*\*Hospitalisation is defined as an inpatient admission, regardless of length of stay, even if the hospitalisation is a precautionary measure for continued observation. Hospitalisations for a pre-existing condition, that has not worsened or for an elective procedure do not constitute an SAE.

\*\*\*Other important medical events that may not result in death, be life-threatening, or require hospitalisation may be considered a serious adverse event/experience when, based upon appropriate medical judgement, they may jeopardise the patient and may require medical or surgical intervention to prevent one of the outcomes listed in this definition.

## **10.2 Recording and reporting**

AEs and SAEs are defined as an event that occurs after the patient has provided written informed consent for trial entry and within 28 days after randomisation.

All AEs which are considered to be related or possibly related to the fracture or immobilisation/no immobilisation will be recorded on the database, including those that fulfil the criteria for being serious (see section 10.1). Unrelated AEs should not be recorded, unless they are deemed as serious. Sites are asked to enter all available information onto the study database as soon as possible after the site becomes aware of the event. Related AEs may be identified by site staff at any point during the study and should be recorded on the adverse event report form, within the participant CRF.

Pain in itself does not need reporting as an AE, unless it meets the definition of being serious.

The below AEs are secondary outcomes, and will be collected from medical records at day 28, and therefore recorded in a separate location on the database. AE report forms are not required for these. If these result in admission to hospital this does not require reporting as an SAE.

- Occurrence of and treatment for pressure ulcers resulting from the use of immobilisation
- Occurrence of and treatment for fracture displacement

SAEs (either related, or not related) will require more detailed information to be recorded on a PDF form. In such cases, the event must also be reported to the Sheffield CTRU within 24 hours of the site becoming aware of the event. The CTRU will coordinate ongoing monthly reporting to the Sponsor, or as soon as possible for an unexpected SAE. All SAEs will be reported, not just those related to the toddler fracture. The CI and/or co-CI will review all reported SAEs to ensure accuracy and consistency.

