## **2.2 Rationale for current study**

Treatment of toddler's fractures via immobilisation of the leg can be associated with other complications. This includes pressure sores, skin breakdown, stiffness of the ankle and knee joint as well as pain from the cast rubbing. Use of immobilisation impacts on activities of daily life for children and their families. It also can lead to delayed recovery from the injury by limiting movement and causing temporary stiffness and weakness of the limb.

The potential advantages of a conservative approach (observation and no immobilisation) are ease of care of the child with a quicker recovery from the injury and no risk of complications from the cast or boot. Avoiding immobilisation allows free movement and prevents the need for frequent visits to check or remove the cast if

used. It prevents stiffness developing in joints that have been rigidly immobilised and potentially allows earlier return to normal activities once pain from the fracture has settled. Toddler's fractures are by definition stable injuries and tend not to displace if not immobilised. Furthermore, in cases where a toddler's fracture is the presumptive diagnosis but a bone or joint infection or minor injury is eventually diagnosed, immobilisation may delay definitive diagnosis.

However, there are concerns that without immobilisation there is a risk of the broken tibia displacing, that more pain is felt during recovery, and a risk of worsening of the injury. The inability to participate in normal activities such as attendance at nursery may also be affected. These may all impact on the child's and carer's wellbeing. Immobilisation allows the limb to be held still, relieving discomfort from the fracture associated with joint movement and maintains the ability to bear weight while the fracture heals.

Despite toddler's fractures being common injuries, there is no universally accepted way to treat these fractures with great variability in management across the UK and the rest of the world due to a lack of well conducted trials. The use of a cast may be an unnecessary treatment that causes discomfort, delayed recovery and unnecessary cost to healthcare organisations. There is therefore a requirement for a large-scale, high-quality randomised controlled trial comparing immobilisation vs no immobilisation.

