#### **10.5 SAE additional reporting**

The Data Monitoring and Ethics Committee (DMEC) and Trial Steering Committee (TSC) will also receive information on all AEs and SAEs, at a frequency agreed with each committee and documented in the appropriate charter/terms of reference.

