## **11.2 Statistical Analysis**

The trial will be analysed and reported according to Consolidated Standards of Reporting Trials (CONSORT) guidelines for noninferiority designs.

The primary endpoint, i.e. FLACC scores, will be analysed using a three-level mixed effects model with randomised treatment, follow-up time point (used as a categorical variable), randomised treatment by time point interaction, baseline FLACC score and minimisation variables as fixed effects, and the post-randomisation FLACC scores at 3 days, day 7 (primary) and day 28 (level 1) nested within participants (level 2), nested within sites (level 3), with random intercepts at level 2 and 3. We shall use restricted maximum likelihood estimation and assume an exchangeable correlation for the covariance structure between the random effects.

The model will be used to obtain the marginal treatment effect (non-immobilisation vs. immobilisation) at 7 days post randomisation. Non-inferiority will be rejected if the upper limit of the 95% confidence interval exceeds the non-inferiority margin of one point in either the as-randomised or per-protocol population. Treatment effects will also be presented for other timepoints.

Sensitivity analyses will assess the potential impact of missing data (including missing not at random scenarios), adherence to the randomised intervention (complier-average causal effects, if appropriate) and area-under-the-curve analyses to summarise cumulative pain over the follow-up. Consistency of treatment effects between important subgroups, including minimisation factors, will be explored.

Secondary endpoints will be analysed using comparable models for continuous and binary endpoints, as appropriate. Time to weight bear will be presented using summary statistics, and compared between groups using a Cox proportional hazards model, adjusted for randomisation factors.

(Serious) Adverse events (i.e. those not included in the secondary outcomes) will be presented descriptively.

Index of Multiple Deprivation (IMD) deciles will be derived from postcodes, and used to explore if treatment preferences and satisfaction differ across different IMD deciles.

Full details of all planned analyses and analysis populations will be collated in a pre-specified statistical analysis plan.

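### Hospital admissions for fracture displacement or pressure ulcers are exempt from SAE reporting, so serious cases lose prompt notification and may not be identifiable in the data

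*Protocol*

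**What the plan says.** Section 10.2 of the protocol handles two harms separately. It calls them AEs but treats them as secondary outcomes, taken from the notes at day 28 and stored apart from the other adverse events. The two are "Occurrence of and treatment for pressure ulcers resulting from the use of immobilisation" and "Occurrence of and treatment for fracture displacement". For both, "AE report forms are not required for these", and "If these result in admission to hospital this does not require reporting as an SAE".

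Other parts of the protocol bear on this:

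- **Section 10.1** lists hospitalisation among the seriousness criteria and counts an inpatient admission of any length, including a precautionary one. Admissions for an unchanged pre-existing condition or an elective procedure are excluded.
- **Section 10.2** also says that every SAE is reported, whether or not it is related to the fracture. It exempts pain from AE reporting only while the pain is not serious.
- **Section 10.3** requires notification within 24 hours and allows for exempt events without listing them.
- **Section 10.5** says that the DMEC and TSC "will also receive information on all AEs and SAEs". **Section 14.2** has the DMEC review safety data and, as needed, critical endpoint data, with unblinded data in closed session.
- **Section 11.2** limits the descriptive safety summary: "Serious) Adverse events (i.e. those not included in the secondary outcomes) will be presented descriptively". Secondary endpoints are analysed with models comparable to the primary one.
- **Section 2.2** explains why displacement matters here: "there are concerns that without immobilisation there is a risk of the broken tibia displacing". It also lists pressure sores among the complications of immobilisation.

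**The concern.** An exemption for events already captured as outcomes is common and usually harmless, because it avoids recording the same minor event twice. This one continues to apply when the event leads to admission, which is the point at which the protocol's own definition calls it serious. The two exempt events are also harms that the rationale links to the choice being randomised.

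What is at stake is prompt oversight and the ability to see severity. A secondary-outcome count of displacements does not tell the reader, the chief investigator or the DMEC how many of those children were admitted, and it is not required until the day-28 note review. The child's clinical care does not depend on trial reporting. The trial's safety oversight does.

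**Working it through.** The plan gives no figure on this point, so the check is mainly a comparison of its sections.

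**1. Does such an admission meet the SAE definition?** Yes under section 10.1, unless it is for an elective procedure or an unchanged pre-existing condition. An unplanned admission for a displaced fracture or a pressure ulcer meets it.

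**2. How are comparable events treated?**

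| Event after consent, within 28 days of randomisation | SAE form and 24-hour notice | Chief-investigator review | In (S)AE summary (11.2) |
|---|---|---|---|
| Admission for an unrelated illness | Yes | Yes | Yes |
| Pain meeting a seriousness criterion | Yes | Yes | Yes, on the natural reading |
| Admission for fracture displacement | No | No | No |
| Admission for a pressure ulcer from immobilisation | No | No | No |

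Pain is the closest comparator: it too is a trial outcome (primary at day 7, secondary at days 3 and 28), yet it becomes reportable once serious.

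**3. What delay is allowed?** For an exempt event on day d after randomisation, the first required capture is the note review, at least 28 − d days later. For d = 3 this is 28 − 3 = 25 days; for d = 10 it is 28 − 10 = 18 days. A non-exempt SAE must be notified within 24 hours of the site learning of it. Parent questionnaires do not fill the gap, since section 9 says that responses are not monitored.

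**4. Can serious cases be recovered from the outcome data?** Not reliably.

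- Section 8.2 collects occurrence and treatment of each event. Its attendance item covers the ED, plaster room and fracture clinic. Inpatient admission is not named.
- The schedule in section 9.1 adds no such item.
- The resource use listed in section 13 covers outpatient, primary, community and social care, and does not name inpatient stays.
- The treatment field may reveal an admission in some cases, but nothing ensures that it does.

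**5. Is there another expedited route?** Section 10.1 defines a notable event, which needs expedited reporting without having to be serious. The protocol assigns no event to that category.

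**6. How do these events reach the DMEC?** Section 10.2 itself calls them AEs, and section 10.5 covers all AEs and SAEs, so they may be included. No section says that the separately stored day-28 data feed the DMEC report, or when.

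**7. Is the wording consistent?** Not fully. Section 10.2 both exempts these admissions and says without qualification that all SAEs are reported. Section 10.3 acknowledges exemptions. The SAE exemption mentions admission only, so the position of a displacement or ulcer that is serious on another criterion, such as lasting disability, is left open.

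**The case against.** The strongest reply is that the exemption is deliberate and does not hide the events. Section 10.2 gives its reason, and section 10.3 carries it forward. The statement that all SAEs are reported can be read as being about relatedness only. Both harms are sought for every child by note review and analysed with between-arm models, whereas other (serious) adverse events are only described. All of this stands, and it rules out several stronger readings.

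- **A reader might infer that these harms disappear from the comparison of arms.** They do not. Sections 8.2 and 11.2 make them analysed secondary outcomes. There is no formal SAE comparison for them to drop out of, only a descriptive summary.
- **A reader might infer that the DMEC does not see them.** No section says so. Sections 10.5 and 14.2 are broad enough to include them, and the DMEC charter, which sets the timing, is not at hand. Only the lack of a stated route is supported.
- **A reader might call both harms arm-specific.** This fits pressure ulcers from immobilisation. Displacement is collected in both arms, although section 2.2 raises the concern for children without immobilisation.
- **A reader might want an expected number of missed SAEs.** The protocol gives no rate of displacement needing admission. With 247 children per arm, an assumed 0.1% gives 247 × 0.001 = 0.25 expected events and an assumed 2% gives 247 × 0.02 = 4.9. That twenty-fold spread only restates the assumption. Sections 2.1 and 2.2 describe these fractures as stable and unlikely to displace, so the low end cannot be dismissed.

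The reply does not answer three things: the loss of prompt notification and review, the missing admission item, and the different treatment of serious pain.

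**Conclusion.** The point holds in a limited form. Section 10.2 removes admissions for displacement or pressure ulcers from SAE reporting although section 10.1 makes admission a seriousness criterion. Such cases lose the 24-hour notice and chief-investigator review, are left out of the (S)AE summary, and may not be distinguishable from minor cases in the outcome data. Their route and timing to the DMEC are not stated.

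The size can be given only as delay: at least 25 days for an admission on day 3, against 24 hours from awareness for any other SAE. This assumes that sites do no more than the protocol requires. The number of children affected is probably small and cannot be derived from the protocol. The between-arm analysis of the two outcomes and the primary non-inferiority conclusion are unaffected. This is a worthwhile, inexpensive improvement in safety reporting; it does not invalidate the design.

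**What to change.** 1. In section 10.2, limit the exemption to displacement and pressure ulcers that meet no SAE criterion, as is already done for pain. Report any that meet a criterion in the usual way.
2. Reconcile this wording with the definition in 10.1, the general SAE statement in 10.2 and the reference to exempt events in 10.3.
3. Record inpatient admission (yes/no, with date) alongside each of these two outcomes in the day-28 note review.
4. In section 11.2, show serious cases by arm in the (S)AE summary, cross-referenced to the secondary outcome so that they are not counted as separate events.
5. State in section 10.5 or 14.2 that DMEC closed reports include both outcomes by arm.

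The cost is a protocol amendment, one data item and probably a few extra SAE forms. The drawback is that the same event appears in two tables, which the cross-reference has to make clear.
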